## 4. Procedure

### 4.1. Description of Interventions

The intervention will be designed and implemented by a sports science professional. All groups in both phases will perform a minimum of 150 min of moderate physical exercise per week or a minimum of 75 min of vigorous exercise per week, always performed under the supervision of a sports science professional. During the intervention participants will progress to 300 min of moderate PA or 150 min of vigorous PA. Prior to the start of the full intervention, participants will undergo a 3-week pre-intervention physical conditioning. Each intervention will last 12 weeks (see Figure 1). Before starting the intervention program, participants will be referred to a physician for medical testing and clearance. During all physical exercise sessions, participants will wear a heart rate (HR) device that will relay their HR to a laptop, from which the sports scientist will be able to control the intensity of the session. The heart rate monitor model to be used is the Polar OH1, which has been validated in previous studies [47]. Polar HR monitors have demonstrated a high level of agreement with the electrocardiogram and can therefore be used as a valid measure of HR in both laboratory and field studies to measure HR during moderate-to-vigorous physical activity (MVPA) [47]. Heart rate will only be measured during the training sessions, with the aim to ensure that the intensity at which the participant performs the exercises is appropriate according to the protocol (it will vary for each intervention arm). Adherence to the intervention will be measured by attendance at the training sessions that make up the intervention.

#### 4.1.1. Phase 1

Three exercise modalities will be compared: (1) AT, (2) AT combined with RT and (3) HIIT. During all intervention sessions, participants will wear an HR monitor connected to a computer. In this way, study staff will be able to control the intensity of the session and individualise exercise prescriptions in real time. Heart rate monitoring will be a key element in ensuring that each exercise is performed at the target intensity, by calculating the intensity at which each volunteer performs the exercise based on a percentage of their HR. Despite there being numerous formulas for estimating the maximum heart ratio (HRmax), studies based on meta-analysis reported that [HRmax = 208 − 0.7 × age] is a more reliable option to predict HRmax [48,49]. Once the HRmax has been estimated, the Karvonen formula will be used to calculate the HR corresponding to a given percentage of intensity. For example, if we want a subject to exercise at 60% of their HRmax, it will be calculated using the Karvonen formula, which takes into account HRmax and basal heart rate (HRB), as follows: HRB + % intensity desired [HRmax—HRB] [50]. This formula has been recommended for both people with cardiac diseases and athletes due to the accurate characteristics of the formula [50].

1)Aerobic Training intervention (AT): Perform 50 min/day, 3 days/week, totalling 150 min/week [34,51] at moderate intensity, as recommended by WHO [26], in a range of 65–75% HRMax. Because any form of aerobic exercise involving large muscle groups and causing sustained increases in HR is likely to be beneficial [52], the type of aerobic exercise will be agreed on with each group of patients, varying from four to eight people. There will be a choice of exercises and participants will be able to choose a combination of up to two different exercises. The participants’ choice of the type of activity to be performed is expected to encourage greater adherence. The range of exercises will be brisk walking or running, swimming and/or aerobic dancing.2)Aerobic Training plus Resistance Training intervention (AT+RT): Perform 50 min/day, 3 days/week, starting with 50% of 1-repetition maximum (1-RM) and follow a progression of increasing loads up to 75% of 1-RM for optimal gains in strength and insulin action [51]. In each session, between five and ten exercises will be worked on, performing 10–15 repetitions, and progressing to 8–10 lifting as the weight increases, involving the major muscle groups from the core, lower body and upper body [53,54]. In all sessions there will be a 3 min warm-up at the beginning of the session and a 2 min cool-down at the end of the session [34].3)High Intensity Interval Training intervention (HIIT): To be considered high intensity, the heart rate needs to be above ≥85% [19,34,55]. Perform 25 min/day, 3 days/week, totalling 75 min/week [34,51] at a vigorous intensity, as recommended by WHO [26]. Starting with four intervals lasting 1 min keeping in a range of 85–90% HRMax, separated by 1 min of low intensity activity (no static) (4 × 1 min intervals), a progression will be followed by increasing the number of circuits, up to ten (10 × 1 min intervals) [19,55,56]. In all sessions there will be a 3 min warm-up at the beginning of the session and a 2 min cool-down at the end of the session [19,34,55,56]. Although the target population is a sedentary population, we expect the HIIT approach, despite being high intensity, to be well received, due to its growing popularity, as demonstrated by a study in which 62% of inactive participants preferred HIIT to other types of exercise [57].4)Participants in the control group will receive written standard PA recommendations in this phase.

#### 4.1.2. Phase 2

Different exercise frequencies per week will be compared using the modality that best controlled blood glucose in phase 1: (1) five sessions/week; (2) three sessions/week and (3) two sessions/week. As mentioned above, all groups in both phases will perform a minimum of 150 min of moderate physical exercise per week or 75 min of vigorous exercise per week, always performed under the supervision of a sports science professional.

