#### 4.2.2. Visit 0 (V0):

Participants will be informed of the exercise modality or frequency to which they have been assigned and the days on which the physical exercise sessions will take place will be agreed upon. During the visit, the participant will wear a heart rate monitor to record their resting heart rate.

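### The AT and HIIT intensities are labelled % of HRmax but calculated as % of heart-rate reserve, so the stated rule does not give the stated ranges

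*Protocol article*

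**What the plan says.** Section 4.1.1 (Phase 1) predicts maximum heart rate as 208 − 0.7 × age. It then gives a general rule: "the Karvonen formula will be used to calculate the HR corresponding to a given percentage of intensity". The worked example ties that rule to a percentage of the maximum: "For example, if we want a subject to exercise at 60% of their HRmax, it will be calculated using the Karvonen formula". The formula is printed as "HRB + % intensity desired [HRmax—HRB" (closing bracket omitted here), where HRB is the basal heart rate.

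The arm descriptions in the same section set the AT target "in a range of 65–75% HRMax", described as moderate intensity, and the HIIT intervals "keeping in a range of 85–90% HRMax". A separate HIIT sentence says "the heart rate needs to be above ≥85" per cent without naming the base. The combined aerobic and resistance arm has no heart-rate range.

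Section 4.2.2 (Visit 0) provides the resting value that the formula needs: "the participant will wear a heart rate monitor to record their resting heart rate". The text shown never mentions heart-rate reserve and never converts between the two scales.

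**The concern.** A percentage of HRmax is p × HRmax. The Karvonen expression is a percentage of the reserve, added on top of the resting rate. The two agree only when the resting rate is zero or p is 100%, so the protocol's rule cannot return the ranges that the protocol states.

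Intensity is part of what distinguishes the Phase 1 arms, and Section 4.1 says heart rate is monitored so that sessions run at the planned intensity. The two readings prescribe different doses:

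- If the % HRmax ranges are literal, applying the formula pushes AT above its stated moderate band and HIIT above its 90% ceiling.
- If Karvonen is meant, the published ranges misdescribe the intervention. A clinician or replicator working from the % HRmax figures would prescribe a lower dose than the trial delivered.

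Phase 2 carries forward the best Phase 1 modality, so the ambiguity can carry forward with it.

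**Working it through.** **Inputs.** From Section 4.1.1: HRmax = 208 − 0.7 × age; target = HRB + p × (HRmax − HRB); AT p = 0.65 to 0.75; HIIT p = 0.85 to 0.90; worked example p = 0.60. From Section 3.2: ages 18–65, so HRmax runs from 208 − 0.7 × 18 = 195.4 to 208 − 0.7 × 65 = 162.5 bpm. The protocol gives no resting-rate value. I assume 70 bpm for illustration and 50–80 bpm for the range.

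**Difference between the two scales.**

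HRB + p(HRmax − HRB) − p × HRmax = (1 − p) × HRB

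This is positive for every resting rate above zero and every p below 100%. As a fraction of HRmax, the formula delivers p + (1 − p) × HRB/HRmax.

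**Illustration: age 50, HRB 70.** HRmax = 208 − 0.7 × 50 = 173; reserve = 173 − 70 = 103.

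| p | As labelled, p × 173 | By formula, 70 + p × 103 | Formula as % of HRmax | Excess, (1 − p) × 70 |
|---|---|---|---|---|
| 0.60 (example) | 103.8 | 131.8 | 76.2% | 28.0 |
| 0.65 (AT lower) | 112.45 | 136.95 | 79.2% | 24.5 |
| 0.75 (AT upper) | 129.75 | 147.25 | 85.1% | 17.5 |
| 0.85 (HIIT lower) | 147.05 | 157.55 | 91.1% | 10.5 |
| 0.90 (HIIT upper) | 155.7 | 162.7 | 94.0% | 7.0 |

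For neither arm does the band from the formula overlap the labelled band. The gap between the top of AT and the bottom of HIIT is 0.10 × 173 = 17.3 bpm as labelled and 0.10 × 103 = 10.3 bpm by the formula.

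**Range over ages 18–65 and HRB 50–80.**

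- Excess: 17.5–28 bpm at p = 0.65; 12.5–20 at 0.75; 7.5–12 at 0.85; 5–8 at 0.90.
- AT limits by the formula: lower 74.0–82.2% and upper 81.4–87.3% of HRmax, against 65% and 75% stated.
- HIIT limits by the formula: lower 88.8–92.4% and upper 92.6–94.9% of HRmax, against 85% and 90% stated.
- Gap between arms: 16.25–19.54 bpm as labelled; 8.25–14.54 bpm by the formula.

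**When the AT bands separate completely.** The formula's lower AT limit exceeds the labelled upper limit when 0.65 × HRmax + 0.35 × HRB > 0.75 × HRmax, that is, HRB/HRmax > 0.10/0.35 = 0.286. The strictest case is age 18: HRB > 195.4 × 0.10/0.35 = 55.8 bpm. At resting rates of 56 bpm or more, the formula's AT band therefore lies wholly above the labelled band at every eligible age.

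**Labelled targets expressed as reserve (age 50, HRB 70).** (p × 173 − 70)/103 gives 41.2% and 58.0% for AT, and 74.8% and 83.2% for HIIT.

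**The case against.** The best defence is that the protocol has one operating rule, and it is Karvonen. Section 4.1.1 states it generally, writes it out, and shows how a percentage target is turned into a heart rate. Visit 0 collects the resting rate, which a simple p × HRmax would not need, and no passage gives p × HRmax as a method. On this reading each participant gets a single bpm band, HRmax is a loose label, and a replicator who reads the whole section would use the right formula. No printed bpm value fails to reproduce. The bpm sizes rest on assumed resting rates. Figure 1 and the supplementary intervention table are not visible and might name the scale.

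Much of this stands. Karvonen is the likelier rule. With one formula for both arms, they stay in order and their bands do not meet. Session length, weekly minutes and interval structure also separate them. Sessions are supervised after medical clearance, and no safety consequence is shown.

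The defence does not remove the error. If Karvonen governs, the published AT and HIIT intensities are on the wrong scale and need correcting. Nor does the visible text show which intensity was chosen for an AT arm described as moderate: 65–75% of HRmax, or the 79–85% of HRmax that the formula gives in the illustration. The unseen material could settle the intention, but it would not make the wording of Section 4.1.1 consistent.

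**Conclusion.** The inconsistency is real and follows from the algebra alone; only its size depends on the resting rate. Under assumed resting rates of 50–80 bpm and ages 18–65, the rule sets AT limits 12.5–28 bpm and HIIT limits 5–12 bpm above the labelled values. It also narrows the heart-rate gap between the arms to about 8–15 bpm from about 16–20. Either the rule or the label is wrong as written, and most probably it is the label. The point bears on how the intervention is defined, delivered and replicated. It does not touch randomisation, the primary outcome, the analysis, sample size, alpha or power. It should be fixed, but it does not undermine the design.

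**What to change.** The exercise lead should state which intensity is intended, and Section 4.1.1 should then use one scale in the rule, the worked example and the arm descriptions. There are three ways to do this:

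- **% HRmax is intended, and kept as the scale.** Compute targets as p × HRmax and drop Karvonen.
- **% HRmax is intended, but Karvonen is kept.** Restate the ranges as % of heart-rate reserve. At age 50 and resting rate 70, the labelled bands correspond to about 41–58% (AT) and 75–83% (HIIT) of reserve. The equivalence shifts with age and resting rate, so the lead must choose fixed reserve ranges.
- **65–75% and 85–90% of reserve are intended.** Keep the numbers and the formula, and replace HRmax with heart-rate reserve in both ranges. Also reconsider whether moderate still describes the AT arm.

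In every case, correct the 60% example, name the base for the 85% HIIT threshold, and check that the monitor bands match. The cost is protocol wording and possibly recalculated monitor settings. No equipment, visits or participants are added.

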### 4.2. Data Collection and Procedures

Data collection (visit −1 and 1) will be performed at the Health Research Institute of the Balearic Islands (IdISBa). Visit 0 and the intervention sessions will be held at the facilities of the University of the Balearic Islands.

In both phase 1 and phase 2, the same number of data collection visits will be carried out and the same information will be collected at each of the visits (Table 1).

#### 4.2.1. Visit −1 (V−1)

Before inclusion in the study, potential participants will be scheduled for a first visit to verify inclusion and exclusion criteria. During this visit, informed consent and baseline data will be collected including sociodemographic data, medication and concomitant pathologies, tobacco and alcohol consumption, assessment of PA, SB, diet, quality of life, quality of sleep, anthropometric and body composition parameters, blood pressure, biochemical blood analysis and gene expression analysis in blood cells. Participants meeting all eligibility criteria will be randomly assigned, stratified by sex, age and obesity, to one of the three intervention groups or control group. The same procedure will be followed for both phases of the study. All participants will be asked to wear an accelerometer, a continuous blood glucose monitor and a daily activities e-diary (intake, sleep, SB and PA) for 14 days to collect accurate baseline PA and blood glucose data.

#### 4.2.2. Visit 0 (V0):

Participants will be informed of the exercise modality or frequency to which they have been assigned and the days on which the physical exercise sessions will take place will be agreed upon. During the visit, the participant will wear a heart rate monitor to record their resting heart rate.

#### 4.2.3. Visit 1 (V1)

Before the follow-up visit (week 15 of intervention), the accelerometer and the continuous glucose monitoring biosensor will be placed for 14 consecutive days, 24 h/d, and participants will complete the e-diary during these 14 days. At the end of follow-up (15 weeks), the accelerometer and continuous glucose monitoring biosensor will be removed. During this visit medication and concomitant pathologies, assessment of PA, SB, diet, tobacco and alcohol consumption, assessment of the quality of life and quality of sleep, anthropometric and body composition parameters, blood pressure, biochemical blood analysis, gene expression analysis in blood cells and adverse events will be collected for all participants (see Table 1).

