### 3.3. Sample Size and Randomization

The sample size has been calculated to detect significant differences in MAGE of at least 1.5 mg/dL and considering a standard deviation of 1.4 mg/dL [45] in any of the three modalities and a dropout rate of 20%, so 30 subjects will be needed in each group, with a sample of 180 participants, 90 in each phase. Furthermore, a control group (30 patients) will be added to evaluate the effect of any type of monitored exercise in these patients versus usual clinical practice. Randomization will be carried out by permuted blocks of eight in a 1:1:1:1 ratio and stratified by prognostic factors: gender, age and obesity using the open-source Oxford Minimization and Randomization (OxMaR) program [46].

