### 5.4. Ethical Considerations

The GLYCEX study will follow the Declaration of Helsinki ethical standards, and all procedures will be approved by the Institutional Review Board of the Balearic Islands Health Service Research Ethics Committee (CEI-IB). The study has been registered on clinicaltrials.gov with the ID NCT05612698 on 4 November 2022. In the event of substantial modifications to the protocol, the Ethics Committee will be informed. All participants will sign a written informed consent, and all data collected will be kept anonymous and confidential. Participants may voluntarily withdraw their informed consent at any time during the study. Data collected prior to patient withdrawal will be retained and used by the study investigators as specified in the informed consent. All participants, before starting the intervention, will undergo a medical examination to certify that they are able to perform physical exercise. No harm or adverse effects are expected given the characteristics of the intervention; however, injuries, such as blows or sprains, derived from the exercise practice, which in no case would suppose a serious risk to the health of the participants, could occur. However, adverse effects, if any, will be recorded and communicated to the CEI-IB.

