## Figures and Tables

**Figure 1 metabolites-12-01286-f001:**
[figure not shown]
Intervention description. Abbreviations: AT, aerobic training; RT, resistance training; HIIT, high-intensity interval training; d/w, days/week; wk, week.

**Table 1 metabolites-12-01286-t001:** Data collection by visits.

	Initial Evaluation	Start	
Visit number	−1	0	1
Time	−Day 7	Day 0	Week 15
Informed consent	X		
Inclusion/exclusion criteria	X		
Randomization	X		
Blood sample	X		X
Glucose monitoring	X		X
Baseline data	X		
Cites management		X	
Adverse events			X
Anthropometric measurements	X		X
Blood pressure	X		X
Physical activity questionnaire	X		X
Sedentary behaviour questionnaire	X		X
Diet, alcohol and smoking questionnaire	X		X
Quality of life questionnaire	X		X
Accelerometer	X		X
Pulsometer		X	

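### The only scheduled adverse event collection is at week 15 (V1); the separate commitment to record adverse effects has no stated time point or mechanism before V1 or at withdrawal

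*Protocol article*

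**What the plan says.** Four places in the protocol article bear on this.

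- **Visit text.** Section 4.2.3 (Visit 1) lists the week 15 assessments and ends: "adverse events will be collected for all participants (see Table 1". Sections 4.2.1 (V−1) and 4.2.2 (V0) do not mention adverse events.
- **Schedule table.** The row "Adverse events" in Table 1 has a single mark. Column alignment is partly lost in the text as read, but the mark sits in the last position (week 15), which agrees with Section 4.2.3. Section 4.2 applies the same visits to both phases.
- **Safety text.** Section 5.4 foresees "injuries, such as blows or sprains, derived from the exercise practice" and says that "adverse effects, if any, will be recorded and communicated to the CEI-IB". It gives no time point, method or responsible role. On withdrawal it says: "Data collected prior to patient withdrawal will be retained and used by the study investigators".
- **Expected dropout and supervision.** Section 3.3 plans for "a dropout rate of 20%, so 30 subjects will be needed in each group". Section 4.1 says that exercise is "always performed under the supervision of a sports science professional". The session data it names are heart rate, and attendance as the measure of adherence.

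**The concern.** A participant who leaves the study before week 15 is not at V1 to be asked. With one scheduled collection point at the end of follow-up, adverse event ascertainment depends on completing the study. Injury is a plausible reason for leaving an exercise trial, so the people whose events are least likely to be collected may be those who had the events that matter most. If such dropout differed between arms, the under-count would differ too, and an arm with more injuries could look safer than it is.

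This matters because the Discussion says the trial will show which modality and weekly frequency best suit adults with prediabetes. The participants are inactive adults with overweight or obesity. Readers will look at the harms of each arm as well as its effect on glucose. Events not recorded at the time cannot be recovered at the analysis stage.

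**Working it through.** The plan states no figure for safety ascertainment, so there is nothing to reproduce. The check compares the passages and then sizes the gap.

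**1. Passages side by side**

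| Source | Time of adverse event collection | Mechanism |
|---|---|---|
| Section 4.2.1 (V−1) | none stated | – |
| Section 4.2.2 (V0) | none stated | – |
| Section 4.2.3 (V1) and Table 1 | week 15 | visit assessment |
| Section 4.1 (sessions) | none stated | only heart rate and attendance named |
| Section 5.4 (ethics) | none stated | recorded and reported to the ethics committee |

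V1 is the only scheduled point. Section 5.4 is broader in intent but is not tied to sessions, withdrawal or any visit. Its rule on keeping data from before withdrawal does not close the gap, because no adverse event data are scheduled before V1.

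**2. Number with no scheduled ascertainment (upper bound)**

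Input: the 20% allowance of Section 3.3. Formula: 0.20 × N, assuming that every dropout misses V1.

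- Per arm: 0.20 × 30 = 6
- Phase 1, four arms: 0.20 × 120 = 24
- Phase 2, three arms: 0.20 × 90 = 18
- Both phases: 24 + 18 = 42 of 210

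Section 3.3 attaches the 20% to the 180 participants in the exercise arms and adds the 30 controls afterwards. On the exercise arms alone the figure is 0.20 × 180 = 36. The 42 also applies the allowance to the control arm.

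**3. Share of injured participants not seen at V1**

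Let r be the injury risk in dropouts divided by that in completers. If V1 were the only source, the share missed would be 0.2r / (0.2r + 0.8).

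- r = 1: 0.2 / 1.0 = 20%
- r = 2: 0.4 / 1.2 = 33%
- r = 3: 0.6 / 1.4 = 43%

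The values of r are assumptions. The article gives no injury rates, so these figures show direction and scale only.

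**The case against.** A reader might infer that injuries in dropouts are lost and that session injuries rest on recall at week 15. The article does not support that, for these reasons.

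- **Table 1 is not a full list of what is recorded.** It has three visit columns and none for sessions. Heart rate is monitored at every session and attendance is recorded there, yet the table shows neither as session data. One mark at V1 therefore does not prove that session injuries go unrecorded.
- **Section 5.4 is a separate commitment** and is not limited to V1. Sessions are supervised, so staff may well note an injury when it happens. No passage says that events are collected by recall.
- **Stopping exercise is not the same as missing V1.** Section 4.2.3 refers to all participants and the main analysis is by intention to treat. Someone who stops training after a sprain may still attend.
- **The planned choice of modality is not affected.** It is made on glycaemic control. Adverse events are not a listed outcome, and no between-arm safety analysis is described.
- **The full protocol may say more.** An article commonly leaves safety forms and withdrawal procedures to it.

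The first four points stand, and they make the figures above upper bounds. The fifth stands only in part: the article is not merely silent, because it fixes a collection point, and that point does not reach participants who leave before it. Supervision alone does not close the gap either. Being present is not the same as recording, and informal noticing would happen only in the exercise arms, which would make comparison with control harder.

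**Conclusion.** The point holds in a limited form. V1 is the only scheduled adverse event collection, and the commitment in Section 5.4 has no stated time point or mechanism before V1 or at withdrawal. Up to about 6 of 30 per arm would have no scheduled ascertainment, and up to 42 of 210 overall. These bounds assume that the 20% allowance is realised and that every dropout misses V1; the total also assumes that the allowance applies to control. The actual loss could be much smaller if staff record session injuries under Section 5.4 or if those who stop exercising still attend V1. The direction is clearer than the size: events that lead to dropout are the most likely to be under-counted. The documents do not support saying that such events will be lost, or that the under-count would change which modality goes forward to phase 2. It should be put right before recruitment, because the data cannot be recovered later.

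**What to change.** Reconcile Section 4.2.3 and Table 1 with Section 5.4 as follows.

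1. Add an adverse event entry to the session attendance record, completed at each supervised session.
2. Add a question at withdrawal, by telephone if needed, on the reason for leaving and on any adverse event.
3. Keep the V1 question, asked in the same words in every arm including control, as the basis for comparing arms.
4. Report session-logged events separately from the V1 responses.

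The cost is one line on an existing form and one question at withdrawal, with no extra visits or staff. The downside is that session logs will capture more events in the exercise arms than in control, which has no sessions. For that reason the common V1 question stays as the basis of comparison and the session log is reported on its own.
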